### Quality control and assurance

All research personnel will receive unified training before the trial commences. The inter-rater reliability, assessed by the intraclass correlation coefficient for scale assessments, must reach ≥0.85 before personnel can participate in formal evaluations. Data entry will employ a double-entry verification mechanism. The research coordinator will be responsible for ongoing data monitoring and review, conducting monthly data integrity checks. At least three neurology and cardiology specialists will jointly supervise the enrollment assessment and diagnostic process. To protect participant privacy, only the research team members, ethics committee, and relevant regulatory authorities will have access to participants' personal information and medical records.

Adherence monitoring: Adherence to rehabilitation training will be monitored using the same threshold as for taVNS/sham stimulation (≥80% of planned sessions), and will be recorded separately from the intervention adherence.

### Statistical methods

Statistical analyses will be performed using SPSS 26.0 and R 4.1.0, following the intention-to-treat principle. All tests will be two-sided, with a significance level of *α* = 0.05 unless otherwise specified for multiple comparisons. Statisticians will remain blinded to group allocation until data lock. All randomized participants will be retained in the intention-to-treat analysis. The per-protocol analysis will report the proportion and characteristics of participants who do not meet the effort criteria. Additional stratified analyses will be considered: (1) all randomized participants; (2) those meeting adequate-effort criteria; (3) those terminating due to cardiopulmonary limitation; and (4) those terminating due to neurological or motor limitation, to assess the robustness of the results. For the primary outcome, VO_2_peak will be analyzed using a linear mixed-effects model, with group, time, and their interaction as fixed effects and participant as a random effect (random intercept) to account for within-subject correlations; a random slope may be added if model fitting requires. Age, sex, baseline VO_2_peak, stroke type, disease duration, baseline National Institutes of Health Stroke Scale score, and recruitment source (hospital or community) will be included as prespecified covariates. In the model, the time factor (T0, T1, T2) is used to estimate longitudinal trends, while baseline VO_2_peak is included solely as a covariate to adjust for baseline differences; the two serve different functions and do not constitute redundant adjustment. The covariance structure will be selected from unstructured, compound symmetry, or first-order autoregressive models based on the Akaike information criterion or Bayesian information criterion. The primary treatment effect will be assessed based on the baseline-adjusted between-group difference in VO_2_peak at T1, and the effect estimate, 95% confidence interval, and corresponding *p*-value will be reported. For secondary outcomes, all four measures (interleukin-6, tumor necrosis factor-alpha, National Institutes of Health Stroke Scale, and modified Barthel Index) will be analyzed longitudinally using the same linear mixed-effects model as for the primary outcome. For variables with substantial deviation from normal distribution or violations of parametric assumptions, generalized linear mixed models or nonparametric methods will be used as supplements. To control for multiple comparisons, a Bonferroni correction will be applied for the four secondary outcomes, with the significance threshold set at *α* = 0.05/4 = 0.0125. The exploratory outcome (heart rate variability) will not be adjusted for multiple comparisons and will be used only for exploratory interpretation. For missing data, the primary analysis will use the linear mixed-effects model under the missing-at-random assumption, utilizing all available observed values. To assess robustness, multiple imputation by chained equations and per-protocol analysis will be conducted as sensitivity analyses. In addition, the originally prespecified repeated-measures analysis of variance will be performed as a complementary analysis for comparison with the primary results; if the sphericity assumption is violated, the Greenhouse-Geisser correction will be applied, and *post-hoc* comparisons will be performed using the Bonferroni method. The incidence of adverse events will be compared using Fisher's exact test. If the sample size permits, prespecified exploratory subgroup analyses will be conducted for stroke type (ischemic vs. hemorrhagic) and recruitment source (hospital vs. community), using interaction tests to assess potential effect modification, with results interpreted only as exploratory. Due to sample size constraints (80 participants per group), stratification was performed only for age and disease duration. Other heterogeneity factors, including stroke type, baseline NIHSS score, and baseline VO_2_peak, have been incorporated as prespecified covariates into the linear mixed-effects model for adjustment.

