#### Secondary outcome measures

Secondary outcomes include: (1) systemic inflammatory markers (IL-6, TNF-α); (2) neurological deficit severity assessed by the National Institutes of Health Stroke Scale (NIHSS); and (3) activities of daily living measured by the modified Barthel Index (MBI). All secondary outcomes will be assessed at T0, T1, and T2. The MBI serves both as an operational basis for rehabilitation intensity adjustment and as a secondary outcome measure. To avoid a feedback loop, the adjusted MBI (accounting for rehabilitation dose) will be used as the primary interpretative measure for this secondary outcome, while the raw MBI will be used only for rehabilitation adjustment and will not serve as a direct basis for outcome interpretation. The NIHSS may have a floor effect in the enrolled population; its score changes will be used only as a safety or exploratory reference and will not serve as a primary efficacy measure.

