### Sample size calculation

The sample size for this study was estimated based on the group-by-time interaction effect for the primary outcome, VO_2_peak. Given the current lack of direct prior data on the effect of taVNS on VO_2_peak in stroke patients, we referred to the standardized effect size (*d* = 0.58) reported in a randomized controlled trial in healthy populations (25). Considering the greater heterogeneity in stroke patients, a conservative moderate effect size assumption was adopted for sample size planning. The sample size calculation was based on the group-by-time interaction from repeated-measures ANOVA, while the primary analysis will use a linear mixed-effects model; the two approaches are consistent in their handling of repeated-measures data, and LMM is more robust to missing data, so the sample size adequacy is unaffected. *A priori* power analysis was performed using the *F* tests—ANOVA: Repeated measures, between–within interaction module in G * Power 3.1 software, with the following parameters: effect size *f* = 0.25, *α* = 0.05, power (1 − *β*) = 0.80, number of groups = 2, number of measurements = 3, correlation among repeated measures = 0.50, and non-sphericity correction *ε* = 0.75. The effect size conversion was based on the formula *f* = *d*/2 (for two-group comparisons), with *d* = 0.58 (healthy populations) converted to *f* = 0.25 (stroke patients). A conservative estimate was adopted considering the greater heterogeneity expected in stroke patients. The assumed correlation among repeated measures (*ρ* = 0.50) was based on the typical range (0.3–0.7) reported in similar stroke rehabilitation studies, taking the median value; the non-sphericity correction (*ε* = 0.75) was set as a conservative value recommended by the G * Power software manual. Under these assumptions, the required total sample size was estimated to be approximately 128 participants, i.e., approximately 64 per group. Accounting for a 20% dropout rate, a final sample size of 160 participants (80 per group) was planned. Given the current lack of direct data on the effect of taVNS on VO_2_peak in stroke patients, this study adopted a conservative estimate based on the effect size from healthy populations; future research may further define the clinically meaningful difference in this population.

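### The secondary outcomes inherit the VO2peak model and its named covariates, and the plan does not say that IL-6, TNF-α and MBI are adjusted for their own T0 values

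*Protocol article*

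**What the plan says.** All from the protocol article.

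- **Secondary outcome model** (Statistical methods): the four secondary outcomes "will be analyzed longitudinally using the same linear mixed-effects model as for the primary outcome".
- **Structure of that model** (Statistical methods): it is specified "with group, time, and their interaction as fixed effects and participant as a random effect (random intercept"). T0 is a response level: "In the model, the time factor (T0, T1, T2) is used to estimate longitudinal trends".
- **Covariates** (Statistical methods): "Age, sex, baseline VO_2_peak, stroke type, disease duration, baseline National Institutes of Health Stroke Scale score, and recruitment source (hospital or community"). The end of the section again names baseline VO2peak and baseline NIHSS as adjustment variables.
- **Role of the baseline term** (Statistical methods): "baseline VO_2_peak is included solely as a covariate to adjust for baseline differences".
- **Treatment contrast** (Statistical methods): "The primary treatment effect will be assessed based on the baseline-adjusted between-group difference in VO_2_peak at T1". No contrast is named for a secondary outcome.
- **Data available** (Secondary outcome measures): "All secondary outcomes will be assessed at T0, T1, and T2". So each outcome's own baseline is collected. The same section adds a rehabilitation-dose adjustment for MBI.
- **Error rate** (Statistical methods): each secondary outcome is tested at 0.05/4 = 0.0125, two-sided.

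**The concern.** For VO2peak, the baseline term in the model is the outcome's own baseline. Carried over unchanged, the same term adjusts IL-6, TNF-α and MBI for a different variable. NIHSS has its own baseline in the list; the other three do not.

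Keeping T0 as a response row does not do the same work. With group, time and their interaction all free and complete data, the fitted T1 group difference is the raw T1 difference, apart from the listed covariates. The T1-minus-T0 interaction is the difference in change. The first gives the T0 value no weight and the second gives it full weight. The efficient weight lies between them and is what adjustment for own baseline estimates.

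At stake are precision at an already strict threshold and sensitivity to chance imbalance at T0. The contrast itself is also open, because the plan names one for VO2peak only.

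**Working it through.** **Inputs.** From Sample size calculation: f = 0.25, hence d = 2 × 0.25 = 0.5; correlation ρ = 0.50, which "was based on the typical range (0.3–0.7) reported in similar stroke rehabilitation studies"; 64 evaluable and 80 randomised per arm. From Statistical methods: two-sided α = 0.0125.

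**Assumption.** d and ρ were planned for VO2peak. The plan gives neither for any secondary outcome, so they are borrowed here and varied.

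**The plan's own figures.** 128/(1 − 0.20) = 160 and 0.05/4 = 0.0125 both reproduce. 64 per arm gives 80.1% power in a two-sample t-test at d = 0.5 and α = 0.05. The repeated-measures interaction test that the plan names does not lead to 128, but that is a separate matter. Here 64 is used only as the plan's evaluable number. The plan states no power for a secondary outcome.

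**Formula.** Two-sample noncentral t with 2n − 2 degrees of freedom and noncentrality (d/√V)·√(n/2), where V is the variance relative to the raw T1 difference:
- raw T1 difference: V = 1
- difference in change: V = 2(1 − ρ)
- adjusted for own baseline: V = 1 − ρ²

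At ρ = 0.5 these are 1, 1 and 0.75. V = 1 supposes that the listed covariates explain none of the outcome.

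**Power at α = 0.0125**

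| n per arm | d | ρ | raw T1 | change | own baseline | gain over raw | gain over change |
|---|---|---|---|---|---|---|---|
| 64 | 0.5 | 0.3 | 61.6% | 44.6% | 66.7% | 5.0 | 22.1 |
| 64 | 0.5 | 0.5 | 61.6% | 61.6% | 76.7% | 15.0 | 15.0 |
| 64 | 0.5 | 0.7 | 61.6% | 86.6% | 92.1% | 30.5 | 5.5 |
| 80 | 0.5 | 0.5 | 73.7% | 73.7% | 86.8% | 13.1 | 13.1 |
| 64 | 0.3 | 0.5 | 20.6% | 20.6% | 28.7% | 8.1 | 8.1 |

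Gains are in percentage points, taken before rounding. A 20,000-run simulation of the random-intercept model (64 per arm, d = 0.5, ρ = 0.5) gave 62.8% for the raw T1 difference, 63.1% for the interaction and 77.3% with T1 adjusted for own baseline.

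**If existing covariates already predict the outcome.** Suppose, for illustration, that they jointly correlate 0.3 with MBI at both T0 and T1. V without own baseline is 1 − 0.3² = 0.91. With it, V is 0.91 − (0.5 − 0.09)²/0.91 = 0.725. Power is 66.7% against 78.3%, a gain of 11.6 points.

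**If own baseline is simply swapped in and T0 stays a free response.** Take unit variances, ρ = 0.5 and the random-intercept model:
- The single baseline slope is (1 + 2ρ)/3 = 2/3.
- The true T1 variance factor is 1 + (2/3)² − 2(2/3)(0.5) = 0.778.
- The model's within-person variance is 1 − ρ = 0.5. Its between-person variance is (2/3 − 4/9) − 0.5/3 = 0.056. So it uses 0.556 at T1.
- The standard error is too small by √(0.778/0.556) = 1.18. A nominal 5% test has size 2Φ(−1.96/1.18), about 10%.

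The T0 rows are partly predicted by themselves, and this pulls down the variance pooled over the three times. Simulation gave 10.0% at nominal 5% and 3.4% at nominal 1.25%. Simulations overall put the 5% test at about 10 to 12%.

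**The case against.** The strongest reply is that the covariate list was written for VO2peak, so using the same model for another outcome naturally means the same structure with that outcome's own baseline. A condensed article may leave such detail to an analysis plan that is not shown. This has weight: the sentence is ambiguous, and nothing in it excludes own baselines. But the article does not merely stay silent. It fixes a named list, extends the model to four other outcomes and repeats baseline VO2peak and baseline NIHSS as the adjusters. The charitable reading also brings a problem of its own, since own baseline as a covariate with T0 as a free response is the structure that inflates type I error.

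Three other objections stand and limit the point:
- A reader might infer that the T0 values of IL-6, TNF-α and MBI are not used at all. The documents do not support that. T0 is a response level, so a change contrast nets it out, though inefficiently.
- A reader might infer bias. Randomisation keeps both the raw T1 difference and the difference in change unbiased; the loss is precision.
- The trial is not powered on these outcomes, and the Mechanistic exploration section limits mechanistic interpretation of the cytokines to exploratory analysis.

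**Conclusion.** The point holds as a matter of specification and precision for the secondary outcomes. The plan should say which baseline covariate and which contrast apply to each of them.

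A loss of 15 points of power should not be quoted as a fact. It depends on d = 0.5, ρ = 0.5, α = 0.0125 and 64 completers per arm, and the first two are VO2peak values. Over the plan's own range of ρ the gain is about 5 to 31 points against the raw T1 difference and 22 down to 6 against the change contrast. At d = 0.3 it is about 8. For MBI it is probably smaller, because baseline NIHSS, age and rehabilitation dose may already explain part of it. In every case computed, adjustment for own baseline was the most precise option.

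A reader might also conclude that the VO2peak model, and with it NIHSS, is in order because the right baseline is in the list. That does not follow. As worded, both keep T0 as a response alongside their own baseline as a covariate, which is the structure shown to be too liberal. The size given here is for the random-intercept model that the plan names. It was not computed for the alternative covariance structures that the plan may select.

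**What to change.** In Statistical methods, replace the statement that the secondary outcomes share the VO2peak model with one of these two, for all four outcomes including NIHSS:

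1. Adjust each outcome for its own T0 value (on the log scale if the outcome is analysed on the log scale), with T1 and T2 as the only responses.
2. Keep T0 as a response and constrain the two group means to be equal at T0. This retains every randomised participant with any data, and so sits better with the plan's intention-to-treat statement.

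Under either option, name the adjusted T1 group difference as the estimate and keep the other listed covariates. Baseline VO2peak may stay or go. Do not add own baseline as a covariate while T0 remains an unconstrained response, and review the VO2peak model for the same reason.

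The cost is one or two sentences of wording and a few lines of code, with no new data or participants. The Ethics and dissemination section plans recruitment from July 2026 and states that no trial data have been examined, so the change can be made before enrolment.

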### Heart rate variability acquisition and analysis

As an exploratory outcome, resting-state electrocardiograms (ECGs) will be recorded before cardiopulmonary exercise testing at T0, T1, and T2. Participants will be placed in a supine position with eyes closed and breathing spontaneously, following a 10 min rest period, between 9:00 and 11:00 a.m., with no caffeine, tea, nicotine, or alcohol intake, and at least 2 h fasting. Using a Healink ECG device (Beijing Hailanxin Medical Technology Co., Ltd., China) with a standard V5 lead (positive electrode placed on the left anterior axillary line at the fifth intercostal space, negative electrode on the right midclavicular line at the first intercostal space), a 5 min ECG will be recorded (sampling rate 250 Hz). Artifacts in the RR interval series will be identified using a custom MATLAB program (RR < 300 ms or >1,500 ms, or a difference >50% from the adjacent RR interval), combined with visual inspection by human reviewers. Ectopic beats (premature atrial or ventricular contractions) will be identified by morphology, and their RR intervals will be replaced by interpolation of adjacent normal RR intervals. If the ectopic beat rate exceeds 5%, the corresponding data segment will be excluded from the primary analysis. Atrial fibrillation not identified at baseline and other rhythms unsuitable for conventional HRV analysis will be flagged as non-analyzable, excluded from the primary HRV analysis, and the proportion of excluded recordings will be reported separately (paced rhythms are already excluded by the exclusion criteria). Quality checks will be performed by two independent research assistants, with arbitration in case of disagreement. Time-domain (SDNN) and frequency-domain (HF, 0.15–0.40 Hz, autoregressive model) indices will be calculated using Kubios HRV Standard software (26). Frequency-domain indices will be natural-log transformed (ln-HF) before statistical analysis, while raw values will be reported as median (interquartile range). As an exploratory outcome, HRV will not be adjusted for multiple comparisons and will be used only for mechanistic interpretation.

HRV analysis will be performed by an independent researcher who is blinded to both group allocation (active vs. sham) and time point (T0, T1, T2). All ECG recordings will be anonymized by removing participant IDs, group information, and time point identifiers before batch analysis, so that the analyst will only see anonymous codes.

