### Mechanistic exploration

To explore potential associations between taVNS-mediated improvement in cardiorespiratory fitness and changes in autonomic function, resting-state electrocardiograms (5 min recordings) will be obtained at T0, T1, and T2. Time-domain (SDNN) and frequency-domain (HF) indices of heart rate variability will be analyzed as exploratory outcomes. These indices will not be subjected to multiplicity correction and will be used solely for exploratory purposes, not for causal inference.

Inflammatory markers (IL-6, TNF-α) remain secondary outcome measures, but their mechanistic interpretation is limited to exploratory analysis. No mediation model is prespecified, and these results will not be used for causal inference.

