### Limitations

This study has several limitations. First, the single-center design and relatively limited sample size may affect the generalizability of the findings. Second, although rigorous blinding procedures have been implemented (participants, clinicians, outcome assessors, and statisticians will remain blinded), the intervention implementers cannot be blinded due to the visibility of the stimulation device, which may introduce potential performance bias. Third, the stimulation parameters have not been fully optimized, and a single parameter combination may not adequately address the heterogeneity of responses across all patients. Fourth, the follow-up period is relatively short (4 weeks post-intervention), precluding assessment of long-term efficacy and preventive effects on hard cardiovascular endpoints after stroke (e.g., cardiovascular death, myocardial infarction, heart failure hospitalization). Fifth, although this study employs a sham stimulation control and incorporates blinding assessment, it remains impossible to completely rule out the possibility that participants may guess their group allocation based on perceived differences in sensation. To monitor blinding effectiveness, participants will be asked about their group guess (active stimulation, sham stimulation, or uncertain) at the end of each week during the treatment period. The proportion of correct guesses will be calculated and analyzed using a binomial test to determine whether it is significantly higher than 50%. If the correct guess rate at any assessment point is significantly higher than 50%, this will be reported as a limitation. It should be noted that this assessment is intended only to monitor blinding effectiveness and cannot substitute for a credible sham stimulation design. Sixth, respiratory rate and tidal volume were not controlled during HRV acquisition, which may affect the accuracy of high-frequency HRV measurements. Both HRV and inflammatory markers are exploratory analytical measures; their results are intended only to explore potential associations and cannot be used for causal inference. In addition, improvement in VO_2_peak is influenced by multiple factors and should not be directly attributed to improvements in autonomic or cardiac mechanisms. Seventh, the study population consists of patients with mild-to-moderate subacute stroke who are able to complete cardiopulmonary exercise testing. Therefore, the results cannot be directly generalized to patients with severe hemiparesis, bedridden patients, patients with substantial cognitive impairment, or those unable to complete CPET. Eighth, this study did not include a specific assessment of lower-limb motor function, and the association between improvements in VO_2_peak and motor recovery remains unclear. Future studies may consider incorporating lower-limb motor function measures, such as the Fugl–Meyer lower extremity scale or the 10 m walk test.

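### The four-outcome Bonferroni family gives NIHSS a share of alpha that its stated role does not need, and the plan does not settle the cytokines' status, the tested visit or the deciding cytokine scale

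*Protocol article*

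**What the plan says.** All from the protocol article.

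- **Family and threshold (Statistical methods).** "a Bonferroni correction will be applied for the four secondary outcomes, with the significance threshold set at" 0.05/4 = 0.0125. The members are IL-6, TNF-α, NIHSS and MBI. The general rule is "All tests will be two-sided, with a significance level of *α* = 0.05 unless otherwise specified for multiple comparisons".
- **Model (Statistical methods).** The four outcomes "will be analyzed longitudinally using the same linear mixed-effects model as for the primary outcome". Where normality clearly fails, generalized linear mixed models or nonparametric methods are added as supplements.
- **Visits.** Secondary outcomes are measured at T0, T1 and T2. T1 as the efficacy time point and T2 as a check of persistence are stated under Primary outcome measure. The T1 contrast in Statistical methods is written for VO2peak only.
- **NIHSS (Secondary outcome measures).** After noting a possible floor effect, the text says "its score changes will be used only as a safety or exploratory reference and will not serve as a primary efficacy measure".
- **Cytokines.** Mechanistic exploration: "Inflammatory markers (IL-6, TNF-α) remain secondary outcome measures", with only their mechanistic interpretation limited to exploration. Limitations: "Both HRV and inflammatory markers are exploratory analytical measures".
- **Transformation.** The only one stated is for heart rate variability: "Frequency-domain indices will be natural-log transformed (ln-HF) before statistical analysis".

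**The concern.** A Bonferroni family should hold the outcomes on which the trial may make a secondary claim, with one named test for each. Four things here are inconsistent or open.

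1. NIHSS takes a quarter of the secondary alpha although its own section gives it no efficacy role. Heart rate variability, the declared exploratory outcome, is left out of the correction.
2. The status of IL-6 and TNF-α depends on the section read. A cytokine p-value of 0.01 would pass the secondary threshold under Statistical methods and be only exploratory under Limitations.
3. No visit or contrast is named for the secondary outcomes. T1, T2 or the group-by-time interaction could each be presented as the result to compare with 0.0125.
4. If the cytokines are clearly non-normal, the plan does not say whether the linear model or a supplementary method decides at 0.0125.

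At stake are secondary power and the freedom to choose a result after seeing the data. The introduction hypothesises favourable changes in inflammatory markers and neurological function, so these results will be read with interest.

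**Working it through.** **1. The plan's figure.** 0.05/4 = 0.0125, which reproduces exactly.

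**2. Familywise error as a function of the number of tests.** For k tests at 0.0125 the Bonferroni bound is k × 0.0125, and under independence the rate is 1 − (1 − 0.0125)^k.

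| Reading | Tests | Bound | If independent |
|---|---|---|---|
| One contrast per outcome | 4 | 0.050 | 0.0491 |
| T1 and T2 both claimable | 8 | 0.100 | 0.0957 |

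A simulation of the eight-test reading (400,000 draws, between-visit correlation 0 to 0.9, between-outcome correlation 0 to 0.5) gave 0.063 to 0.096. The correlations are assumptions, since the documents give none for the secondary outcomes. Holding 0.05 over eight tests would need 0.05/8 = 0.00625 each.

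**3. What the NIHSS share costs.** The documents power VO2peak only, so all secondary effects below are assumed. Inputs: 64 per arm (Sample size calculation, before the dropout allowance), a baseline-to-follow-up correlation of 0.5 borrowed from the same section, and d = 0.40 for IL-6, TNF-α and MBI.

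- Standard error in SD units: √(1 − 0.5²) × √(2/64) = 0.866 × 0.1768 = 0.153.
- Expected z: 0.40/0.153 = 2.61.
- Four-outcome Bonferroni, two-sided 0.0125, critical z 2.498: power = Φ(2.61 − 2.498) ≈ 55%.
- Three-outcome Bonferroni, 0.05/3 = 0.0167, critical z 2.394: power = Φ(2.61 − 2.394) ≈ 59%.
- Three-outcome Holm at 0.05, by simulation with independent outcomes: about 68% per outcome.

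So removing NIHSS alone gains about 4 points, and most of the rest comes from Holm. An unadjusted two-sample t-test at d = 0.50 and 64 per arm shows the same modest first step: 0.62 at 0.0125 and 0.66 at 0.0167.

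**4. Cytokine scale.** Assumptions: lognormal concentrations, a true 30% reduction (ratio 0.7), baseline-adjusted analysis, 64 per arm, correlation 0.5 on the log scale, alpha 0.0125. Simulated power:

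| Assumed log-SD | Raw scale | Log scale |
|---|---|---|
| 0.6 | 81% | 91% |
| 0.8 | 43% | 65% |
| 1.0 | 21% | 43% |

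These figures are good to a point or two of simulation error. In a separate simulation of unadjusted t-tests with no true effect, the raw-scale type I error at nominal 0.0125 was 0.0125, 0.0116, 0.0096 and 0.0074 for log-SD 0.5, 0.7, 0.9 and 1.1. Skew therefore costs power and does not inflate error.

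**The case against.** The strongest reply is that the multiplicity rule is valid as written. It gives one share to each of four outcomes, and the secondary outcomes use the same model as the primary outcome, whose effect is read at T1. On that reading there are four tests and familywise error is at most 5%. Nothing says that T1 and T2 may both be claimed at 0.0125. This stands: a reader might infer that secondary error is not controlled at 5%, but the documents do not support that as a fact. What remains is that the T1 contrast is never written for these outcomes, although the article commits itself to a numerical threshold that depends on it.

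A reader might also infer that three of the four tests are wasted. They are not. Mechanistic exploration expressly keeps the cytokines secondary, and the contrary sentence in Limitations sits in a passage about causal inference. That is a wording conflict, and only NIHSS is plainly misplaced. Nor can one count the cytokines out of the family and still count all eight contrasts. With MBI alone, two visits at 0.0125 give at most 2 × 0.0125 = 2.5%; with only NIHSS removed, six give at most 6 × 0.0125 = 7.5%.

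Finally, a reader might infer that the plan mishandles skewed cytokines. The documents give no cytokine distribution, the plan has a provision for non-normality, and choice of scale is often left to an analysis plan. That also stands in large part. The narrower point is that the provision is only supplementary and leaves the deciding result unnamed. Holm in place of Bonferroni is an improvement and does not correct an error.

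**Conclusion.** The point holds as a set of inconsistencies with a modest cost. It is minor, because the primary endpoint and its test are unaffected.

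- **Needs no outside assumption:** NIHSS holds a confirmatory share against its stated role, the article contradicts itself on the cytokines, and no tested contrast is named for the secondary outcomes.
- **Conditional:** error above 5% arises only if two visits per outcome can be claimed at 0.0125. It could then reach about 9.6%, less with correlated tests. With one contrast per outcome it is at most 5%.
- **Illustrative:** the gain from about 55% to about 68% assumes d = 0.40 on all three remaining outcomes, 64 per arm and correlation 0.5. The log-scale gain of roughly 10 to 22 points depends on assumed lognormal data with log-SD 0.6 to 1.0.

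**What to change.** 1. In Statistical methods, remove NIHSS from the confirmatory family and report it descriptively, in line with Secondary outcome measures.
2. Reword the Limitations sentence to agree with Mechanistic exploration: IL-6 and TNF-α are secondary outcomes, and only their mechanistic interpretation is exploratory.
3. State that IL-6, TNF-α and MBI are each tested once, on the baseline-adjusted between-group difference at T1, with Holm at a familywise 0.05. Report T2 as descriptive evidence of persistence.
4. Make the natural-log scale the deciding analysis for IL-6 and TNF-α, reported as ratios of geometric means with confidence intervals. Keep other methods as sensitivity analyses.

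The cost is wording, with no change to sample size or procedures, and recruitment is not planned to start until July 2026. The downsides are that cytokine effects appear as ratios, NIHSS carries no formal claim, and simultaneous confidence intervals are less simple under Holm than under Bonferroni.
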